##### Mean change from baseline in consumption of acute migraine medication (analgesics or triptans) measured in days with acute headache medication use during the last 4 weeks of the intervention

The same headache diary in pen and paper form is used to record the change in days with acute headache medication use (analgesics or triptans). With this approach the number of tablets is not of primary interest, but rather the number of days on which one or more analgesics or triptans were consumed. A clinically meaningful migraine preventative is predicted to lower the days during which migraine acute medication is necessary.

##### Mean change from baseline in migraine intensity (measured with a numerical rating scale from 1 to 10) during the last of 4 weeks of the intervention period

The same headache diary in pen and paper form is used to record a potential change in migraine intensity, as measured with a numerical rating scale from 1 to 10. Each migraine or headache day, respectively, is given an intensity score, with 0 being not painful at all and 10 being an operation without anaesthesia.

##### Change in disability from baseline during any treatment period, as assessed with the Migraine Disability Assessment and the Headache Impact Test (comparison baseline and post-intervention score)

In order to assess a change in migraine and headache-related disability, two commonly used validated and reliable questionnaires are used: the Migraine Disability Assessment (MIDAS) and the Headache Impact Test (HIT-6) [59–63]. The German translations were also shown to have adequate reliability and validity [60, 63]. Both questionnaires will be provided as pen and paper versions and will be filled out at the baseline visits (V2 and V5) and the end of innervation visits (V4 and V7), respectively.

#### Exploratory outcome measures

The demographic characteristics and neurological examination will be assessed at one time point (Visit 1). To determine the potential mechanisms of action of successful migraine treatment, we are going to examine single nucleotide polymorphism (SNP) markers in order to assess the genetic background of migraine patients involved in this study. In addition to this, we also plan to conduct gene expression analysis. SNP and gene expression analysis will be conducted using microarrays. In our analysis strategy we especially focus on, but not limit to, genes coding for mitochondrial-related enzymes (citrate synthase, cytochrome C oxidase subunit 1, succinate dehydrogenase subunit A).

We will also examine the serum concentration of oxidative and nitrosative stress markers (malondialdehyde (MDA), carbonylated proteins, nitrate, nitrite, nitrotyrosine) using enzyme-linked immunosorbent assay (ELISA) and mass spectroscopy. In addition to Hba1c, insulin, cortisol, lactate and markers of functioning, cytokines will be analysed using the MILLIPLEX MAP Human Cytokine/Chemokine Magnetic Bead Panel—Premixed 41 Plex—Immunology Multiplex Assay.

Optionally, patients will also receive an Abbott FreeStyle Libre Blood Glucose Monitoring System for 2 weeks at visits V2, V3, V5 and V6, respectively, which will allow permanent tissue glucose monitoring without finger pricking. This allows us to examine a potential association between blood glucose levels (hyperglycaemia or hypoglycaemia) and migraine, and the potential effect of the study medication on glucose levels.

### Safety outcomes measures

Safety and tolerability will be determined by:comparison of treatment-emergent adverse events (any event regardless of potential causality with the drug) and treatment-related adverse events (such as gastrointestinal upset) as imputed by the principal investigator between active treatment and placebo; andexamination for potential effects of the intervention on routine laboratory parameters (renal and liver function tests, electrolytes, full blood count, lipids, glucose, CRP, Hba1c, insulin, cortisol, lactate, TSH, FT4 and FT3) in the treatment group compared to the control group.

### Study procedure

At screening (Visit 1 (V1), week − 4), patients are informed about preclinical data, alternative treatments, potential risks and benefits of the study (see Fig. 2). Further, written informed consent, including consent for the collection of blood for genetic analysis, from the patients is obtained by the trial physician. After signing the informed consent form, the inclusion and exclusion criteria are verified. If the criteria are fulfilled, the patient will be enrolled in the study under reserve. During V1 the following additional procedures are performed: a detailed first clinical interview/examination, vital signs, migraine diary explanation, where necessary a pregnancy test and a neurological examination. After screening, visits will be scheduled for baseline (V2, week 0). V1 will last approximately 30 min.

**Fig. 2 Fig2:**
[figure not shown]
Detailed study schedule. ^1^Blood pressure, heart rate, weight and height. ^2^Pen and paper headache dairy. ^3^Migraine Disability Questionnaire (Migraine Disability Assessment (MIDAS)) and Headache Impact Test (HIT), German versions, standard questionnaires for assessing the extent of migraine-related disability. ^4^Blood beta-hydroxybutyrate and glucose levels, measured with a portable ketone meter (precision xtra by Abbot). ^5^Routine laboratory (renal and liver function tests, electrolytes, full blood count, C-reactive protein, serum cholesterol, triglycerides, serum proteins, albumin, glucose, Hba1c, insulin, cortisol, lactate, TSH, FT4 and FT4). ^6^Blood draw (1 × EDTA, 1 × PAXgene) at each time point for genetic profiling and gene expression analysis using microarrays. ^7^Blood draw at each time point for oxidative and nitrosative stress markers (malondialdehyde (MDA), carbonylated proteins, nitrite, nitrotyrosine) and serum cytokine measurements (including, but not limited to, IFN-γ, IL-1β, IL-2, IL-4, IL-5, IL-6, IL-10, MCP-1, TNF-α, TNF-β, TGF-β1). V = visit

At the start of the intervention (baseline/V2, week 0) the following procedures are performed: check inclusion/exclusion criteria and, if met, confirmation of enrolment, migraine diary check, diet check, consumption of first dose of IMP/placebo, adverse events, vital signs, physical examination if necessary, blood draw (for safety, biomarkers and genetic analysis), standardised migraine questionnaires, KB and glucose concentration measurements using a portable point-of-care blood ketone meter (precision xtra from Abbot) and/or the Abbott FreeStyle Libre Blood Glucose Monitoring System. Patients will be randomly assigned to the treatment or control group and receive the according study medication, which will be consumed three times daily for the following 12 weeks. V2 takes approximately 60 min.

After 4 weeks of intervention, there will be another visit (V3, week 4), during which KB and glucose levels will be measured, adverse events will be recorded, vital signs, diet and migraine diary will be checked, a dose of IMP/placebo will be consumed, blood for safety will be drawn, physical examination will be performed if necessary, participants will be provided with the rest of the study medication for the first intervention period and sachets of used study medication will be collected for compliance control. V3 takes about 30 min.

During the visit after the first intervention period (V4, week 12), the following procedures are performed: migraine questionnaires, migraine diary and diet check, consumption of IMP/placebo, KB and glucose measurements, vital signs, blood draw for biomarker and safety analysis, physical examination if necessary and sachets of used study medication will be collected for compliance control. V4 takes about 60 min.

After 8 weeks without intervention, V5 (week 20) takes place, which is identical to the baseline visit (V2). V5 includes the following procedures: standardised migraine questionnaires, migraine diary and diet check, consumption of IMP/placebo, blood draw for biomarker and safety analysis, physical examination if necessary, KB and glucose concentration and vital signs. At this visit the patients will receive the alternative treatment to the first intervention.

After 4 weeks of the second intervention, V6 (week 24, analogous to V3) takes place. The following procedures are performed: migraine diary and diet check, consumption of IMP/placebo, KB and glucose measurements, adverse effects, vital signs, blood draw for safety and physical examination, if necessary. Participants will be provided with the rest of the study medicament and sachets of used study medication will be collected for compliance control. V5 takes about 30 min.

After completion of the second intervention, the last visit (V7, week 32, analogous to V4) takes place. The following procedures are performed: migraine questionnaires, migraine diary and diet check, consumption of IMP/placebo, KB and glucose measurements, vital signs and blood draw for biomarker and safety analysis, physical examination if necessary and collection of sachets of used study medication for compliance control.

All investigations will take place at the clinical trial unit of the University Hospital Basel, Switzerland. Participants are required to keep a detailed headache diary for the entire duration of the study.

### Sample size estimation

#### Determination of sample size

Sample size is estimated to be able to show the superiority of IMP over placebo. A crossover design with 1:1 IMP/placebo:placebo/IMP randomisation is planned.

#### Fixed sample size estimation

##### Assumptions

Sample size estimation is based on the following assumptions:We expect the baseline number of migraine days per 4 weeks to be 10 days in our patient population.Placebo effect: based on recent findings [64], we assume a rather strong placebo effect of 32% reduction in the primary endpoint. This corresponds to an absolute reduction of 3 migraine days per 4 weeks.IMP effect: synthesising previous findings [4, 64] and our pilot data [65], we aim to detect a difference of 2 days between placebo and IMP.We assumed the absolute reduction in migraine days to be normally distributed with a standard deviation of 3 days.We assume a conservative intra-patient correlation between IMP and placebo of 0.4.Drop out: a high drop-out rate of 30% is assumed.

##### Re-sampling

The sample size was estimated using a re-sampling method. Each sample size (n_i_ = 1,...,49 = 12, ..., 60) was evaluated by sampling *R* = 999 times the reduction in migraine days from a bivariate normal distribution as already described. For each sample, whether superiority of the IMP over placebo could be shown (i.e. whether a two-sided paired *t* test resulted in significant *p* < 0.05) was tested.

In order to show the superiority of the IMP over placebo with a statistical power of 90%, 45 patients should be recruited in total to ensure 31 evaluable patients, assuming a drop-out rate of 30%. Figure 3 shows how the sample size depends on the expected reduction in number of migraine days in the IMP arm.

**Fig. 3 Fig3:**
[figure not shown]
Sensitivity of sample size with regard to expected difference in reduction in number of migraine days per 4 weeks of IMP compared to placebo. Example given, based on an effect size of 2 and a statistical power of 90%. The curves are smoothed and are for illustrative purposes only

### Recruitment

Patients will be informed about the study at the Department of Neurology, University Hospital Basel (USB). Moreover, there will by flyers publicly displayed in the waiting room of the neurology and general medicine department of the University Hospitals in Basel, Bern, Zurich and St Gallen, as well as the University Library. An announcement similar to the flyer will be posted on the webpages of the University of Basel “Marktplatz” dedicated to research studies (https://markt.unibas.ch/nc/inserate/kategorie/job-angebot-studien/) as well as the USB website (https://www.unispital-basel.ch/lehre-forschung/studieninserate/) and the University Children’s Hospital Basel (UKBB) website (http://www.ukbb.ch/en/research/research-groups/neuromuscular-research.php), respectively. More flyers will be displayed in local pharmacies and pharmacies in Germany (with a radius of approximately 100 km around Basel), local neurologists, the neurological department of the Bruderholzspital (Kantonsspital Baselland) and the Headache Clinic of RehaClinic, located in Baden as well as Bad Zurzach, and also in the neurological outpatient clinic in Brugg (team of [name]). Flyers will also be displayed in local busses and trains. The Swiss Headache Society (SKG) and the German migraine and headache society (DMKG) will advertise the trial on their website. All websites may include the link to a short recruitment video (https://www.youtube.com/watch?v=2YzNjIXk_eY&t=19s) explaining the clinical trial with similar wording to the flyer. The video and an advertisement with similar wording to the flyer will also be advertised on Facebook (for users in a radius of 200 km of Basel). Patients previously contacted for a migraine–sport intervention study at the USB (EKNZ-Number 194/13) will be contacted again, if they previously agreed and met the inclusion criteria for the current study.

### Randomisation and blinding

#### Methods of minimising bias

Bias will be minimised by randomisation in 1:1 allocation and blinding of patients and investigators to the intervention. Randomisation will be done using an electronic data capture (EDC) system (SecuTrial) through an independent individual. The medication will be numerically labelled at the Pharmacy of the University Hospital of Basel and will then be provided to the ward and applied to the patient. This will allow a double-blinded randomisation (patient and treating physician will be blinded to the treatment).

The placebo powder has the same texture, colour and packaging as the IMP, so they cannot be distinguished in their appearance. The placebo also has a similar side-effect profile to the IMP. Data will be checked for protocol violation by the independent monitoring institution (see Quality assurance and control).

#### Randomisation

A crossover design with 1:1 AB/BA (IMP/placebo:placebo/IMP) randomisation is planned. The randomisation list will be computer generated and uploaded into the electronic data capture software SecuTrial by the responsible Data Manager at the Clinical Trial Unit (CTU) of the University Hospital Basel. Only unblinded personnel at the Pharmacy of the University Hospital Basel and at the CTU Basel will have access to the randomisation list. Just before the baseline visit, a clinical investigator will use SecuTrial to automatically assign a randomisation number from the randomisation list to the patient.

An additional list with medication numbers complementing the treatment arm of the first intervention period will be provided by the CTU, in order to allow opposite treatment allocation during the second intervention period without unblinding the trial staff.

#### Blinding procedures

The study medication (IMP or placebo) will be provided as similar-looking medication in sachets. The medication will be packed by the Pharmacy of the University Hospital of Basel and will be numerically labelled using the randomisation list provided by the responsible Data Manager at CTU Basel. All investigators and patients will remain blinded until the trial is completed and the database has been locked.

#### Unblinding procedures (code break)

In the case of problems and safety concerns that cannot be solved with ongoing randomisation, the participant’s allocated intervention will be revealed. Unblinding can be performed by authorised investigators using the EDC software SecuTrial. Each unblinding is documented in the EDC’s integrated audit trail system and automatically reported to the principal investigator.

### Data management

The study data recorded in the CRF will be transferred to a corresponding electronic CRF (e-CRF) by the clinical investigators. The principal investigator and co-investigator at the study site will be responsible for assuring that the data entered into the e-CRF is complete and accurate, and that the entry and updates are performed in timely manner. All information recorded in the e-CRFs will be traceable to the source documents in the patient’s file and in the date source files.

#### Data management system

Data management will be conducted fulfilling all ethical and legal requirements according to Good Clinical Practice (GCP) and the Swiss Laws as “Bundesgesetz über die Forschung am Menschen” (Humanforschungsgesetz (HFG)).

The e-CRF will be implemented by the data management group at the Clinical Trial Unit (CTU) of the University Hospital Basel using the electronic data capture (EDC) software SecuTrial. The EDC system runs on a server maintained by the IT department of the University Hospital Basel.

Data entry will be performed by trained clinical investigators at the UKBB.

#### Data security, access and back-up

The EDC system is accessible via a standard browser on a www-connected device. Password protection and user-right management ensures that only authorised UKBB or CTU staff can enter the system to view, add or edit data according to their permissions. User administration and user training is performed by the CTU Basel according to predefined processes.

Back-up of SecuTrial study data is performed regularly according to the processes of the IT department of the University Hospital Basel. An integrated audit trail system will maintain a record of initial entries and changes made, reasons for change, time and date of entry, and user name of the person authorising entry or change.

Source data will be available at the site to document the existence of the study participants and will include the original documents relating to the study (patient demographics, medical history, medication, neurological examination, informed consent forms).

#### Analysis and archiving

The EDC system will be locked after e-CRF data entry is completed, all data have been monitored and raised queries have been resolved. The complete study dataset is exported from the database and transferred to the study statistician as well as the principal investigator through a secure channel. The exported data will be archived for 10 years by the principal investigator.

#### Electronic and central data validation

Data entered into the e-CRF will be validated for completeness and discrepancies automatically. The data will be reviewed by the responsible investigator as well as an independent monitor. The monitor will raise queries using the query management system implemented in SecuTrial. Designated investigators have to respond to the query and confirm or correct the corresponding data. Thereafter, the monitor can close the query.

#### Data monitoring

To ensure the quality of the study conduct and of the data, monitoring of the study is performed by organisations independent of the study (CTU, USB and Kammermann Monitoring Services GmbH). All inclusion and exclusion criteria are checked, and the monitor controls whether the data have been recorded correctly in the CRF, whether the drug accountability is correct and whether serious adverse events (SAEs) have occurred during the study.

### Statistical analyses

Detailed methodology for summaries and statistical analyses of the data collected in this study will be documented in a statistical analysis plan. The statistical analysis plan will be finalised before database closure and will be under version control at the CTU, University Hospital Basel.

The primary endpoint, the number of migraine days in the last 4 weeks of treatment, will be measured twice for each patient, once after the placebo treatment period and once after the IMP treatment period. The number of migraine days in the 4 weeks before the start of treatment will be assessed for both treatment periods, thus there will be two baseline values that will be used as covariates. This process has the aim of correcting for any potential seasonal variation in baseline migraine frequency or carry-over effects.

#### Hypothesis

The *null hypothesis* is that there is no difference in the difference in number of migraine days per 4 weeks from baseline to the last 4 weeks of intervention between the IMP and the placebo treatment.

The corresponding *alternative hypothesis* is that the difference in the number of migraine days per 4 weeks from baseline to the last 4 weeks of intervention differs between the IMP and the placebo treatment.

#### Statistical criteria for termination of trial

No early stopping is planned, either for efficacy or for futility.

#### Planned analyses

##### Datasets to be analysed, analysis populations

The full analysis set (FAS) consists of all patients who are randomised and for whom the number of migraine days per 4 weeks at baseline is available.

The intention to treat (ITT) will include all randomised patients for whom the number of migraine days of at least the first 4 weeks of the first treatment period is available.

The per protocol (PP) will include all patients from the ITT set for whom the primary endpoint is available for both treatment periods, who are compliant as per the protocol (see later) and who have no protocol violations (to be defined in detail in the statistical analysis plan).

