### Interventions

#### Experimental intervention

The investigational medicinal product (IMP) used in this clinical trial is d-l-beta-hydroxybutyrate (βHB) in powdered calcium (Ca^2+^)–magnesium (Mg^2+^)–salt form (Ca-Mg-βHB). d-l-Beta-hydroxybutyrate calcium salt (Ca-βHB) dissolves in water (i.e. in the body) into Ca^2+^ and d-l-beta-hydroxybutyrate (βHB), the compound of interest. d-l-Beta-hydroxybutyrate magnesium salt trihydrate (Mg-βHB) dissolves in water (i.e. in the body) into Mg^2+^ and βHB. Also known as beta-hydroxybutyric acid, 3-hydroxybutyric acid or 3-hydroxybutyrate, βHB is an endogenous metabolite with the formula CH_3_CH(OH)CH_2_CO_2_H. It is a beta-hydroxy acid and a keto acid. The IMP was purchased from Ergomax (https://www.ergomaxsupplements.com) in bulk powder of GMP quality and packaged at Hänseler AG (Herisau, Switzerland). It does not contain anything else other than the βHB mineral salts. The flavour is masked using a sucralose-based sugar-free syrup. The daily dose of 9 g Ca-βHB contains 7.54 g of βHB and 1.47 g Ca^2+^, and will be divided into three servings supplied in individual sachets containing 2.51 g βHB and 0.49 g Ca^2+^, respectively. The daily dose of 9 g Mg-βHB contains 6.6 g βHB and 0.77 g Mg^2+^, and will also be divided into three servings supplied in individual sachets containing 2.2 g βHB and 0.26 g Mg^2+^. Both IMPs are provided as a water-soluble powder. During the 12-week intervention period participants will consume the IMPs in three oral doses, to be taken with or after breakfast, lunch and dinner, respectively. This adds up to less than 100 kcal per day. Each serving will raise KB levels for approximately 3 h. To minimise possible gastrointestinal symptoms such as bloating or diarrhoea, patients are instructed to increase the dosage over time, starting with half the dose during the first week before reaching the maximum dosage by day 7.

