##### Primary analysis

The primary endpoint, the number of migraine days in the last 4 weeks of treatment, will be measured twice for each patient, once after the placebo treatment period and once after the IMP treatment period. The number of migraine days in the 4 weeks before start of treatment will be assessed for both treatment periods, thus there will be two baseline values that will be used as covariates. This process has the aim of correcting for any potential seasonal variation in baseline migraine frequency or carry-over effects.

The primary analysis will be performed using a linear, mixed-effects regression model. The primary model will include the primary endpoint (the number of migraine days in the last 4 weeks of treatment) as the response variable, the respective baseline value as a covariate, treatment (IMP vs placebo) and period (first vs second) as main effects, the two interaction terms “treatment × period” and “treatment × baseline value”, and patient as random effects. A significant interaction term between treatment and period would indicate a carry-over effect. Since it is not known how strongly the primary endpoint correlates with the baseline value, it is not known whether including the baselines as covariates in the model is sensible. Therefore, the already described primary model will be compared to models without the interaction term “treatment × baseline value” and without both the interaction term “treatment × baseline value” and the baseline value as a covariate by means of Akaike’s Information Criterion (AIC).

The primary analysis will be done on the ITT set.

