#### Handling of missing data and drop-outs

The frequency of, timing of and reasons for, as well as all side-effects of, drop-outs will be reported for each treatment. Patients who drop out during the first run-in period or during the first 4 weeks of the first treatment period will be excluded. All patients who drop out later will be included in the ITT set.

For patients who drop out after the first 4 weeks and before the end of the first treatment period, the primary endpoint for the first treatment period will be imputed using multiple imputations. If appropriate, imputations will be accounted for baseline value and number of migraine days during the first treatment period, as far as available. The primary endpoint for the second treatment period will not be imputed for these patients.

For patients who drop out after the end of the first treatment period and before the first 4 weeks of the second treatment period are finished, the primary endpoint for the second treatment period will not be imputed. The primary endpoint for the first treatment period will be available.

For patients who drop out after the first 4 weeks and before the end of the second treatment period, the primary endpoint for the second treatment period will be imputed as already described.

Thus, for each patient included in the ITT set, the primary endpoint will be available (whether measured or imputed) for at least the first treatment period and will be taken into account with the proposed mixed effects models.

In case there are indications for missing data not at random, the inverse probability of censoring weights (IPCW) will be considered.

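### The set labelled ITT leaves out randomised, dosed patients who leave before 4 weeks of period-1 diary data exist, and no planned efficacy analysis brings them back

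*Protocol article*

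**What the plan says.** Datasets to be analysed, analysis populations, defines three sets.

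- Full analysis set, which requires only a recorded baseline count: "The full analysis set (FAS) consists of all patients who are randomised and for whom the number of migraine days per 4 weeks at baseline".
- ITT, which requires recorded counts from the start of period 1: "The intention to treat (ITT) will include all randomised patients for whom the number of migraine days of at least the first 4 weeks".
- Per protocol, which also requires compliance and no protocol violations: "The per protocol (PP) will include all patients from the ITT set for whom the primary endpoint is available for both treatment periods".

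Handling of missing data and drop-outs states the ITT condition as an exclusion: "Patients who drop out during the first run-in period or during the first 4 weeks of the first treatment period will be excluded". Later drop-outs stay in. Multiple imputation of a period's endpoint is planned only for patients who passed the first 4 weeks of that period.

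On use of the sets, Primary analysis states: "The primary analysis will be done on the ITT set". Secondary analysis and Exploratory analyses name the same set. Subgroup analyses add terms to the primary model. Sensitivity analysis repeats the main analysis on the per-protocol set. No analysis is assigned to the full analysis set.

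**The concern.** An intention-to-treat set should be fixed by randomisation. This one depends on something observed in the 4 weeks after it, while patients are taking a randomised product. The article itself foresees treatment-related reasons to leave in that window. For the active product, Experimental intervention says: "To minimise possible gastrointestinal symptoms such as bloating or diarrhoea, patients are instructed to increase the dosage over time". Control intervention says that mannitol can also cause gastrointestinal symptoms, and Safety assessments provides for stopping intake after laboratory changes or serious adverse events.

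Whether a given patient is in the set can therefore depend on allocation. Someone who would leave within 4 weeks on the active product disappears if randomised to it first. Randomised to placebo first, the same person completes period 1, leaves early in period 2 and stays in the set with a measured placebo outcome.

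The headline result would carry an ITT label that its definition does not support. No planned analysis would show the consequence, because the only sensitivity set is drawn from the same filtered set.

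**Working it through.** **Who is in which analysis.** Take a patient randomised at V2, with a baseline count, who leaves the study in week 2 of period 1.

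| Set | Includes this patient? | Analyses assigned |
|---|---|---|
| Full analysis set | yes | none |
| ITT | no | primary, secondary, exploratory |
| Per protocol | no (nested in ITT) | sensitivity |

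So no planned efficacy analysis includes the patient.

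**The plan's own figure.** Inputs from Assumptions and Re-sampling: difference 2 days, SD 3, within-patient correlation 0.4, two-sided paired t test at 0.05, power 90%, drop-out 30%. SD of the difference = 3 × √(2 × (1 − 0.4)) = 3.286. Exact power from the noncentral t distribution is 0.896 at n = 30 and 0.906 at n = 31, so 31 are needed. Then 31 / 0.7 = 44.3, rounded up to 45. Both stated figures reproduce. They concern evaluable patients and are not affected by this point.

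**How many patients could be lost.** Planned drop-out is 45 × 0.30 = 13.5. The share falling in the first 4 weeks of period 1 is not given, so it is assumed:

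- one third to one half early: 13.5 / 3 = 4.5 to 13.5 / 2 = 6.75 patients, or 10% to 15% of 45;
- 10% to 100% early: 1.35 to 13.5 patients, or 3% to 30%.

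**How far the estimate could move.** Assumed scenario: 22 active-first patients, of whom 4 leave early with no benefit over placebo; all others gain 2 days; no early leavers in the placebo-first sequence. Outcomes are written as benefit over placebo, and the leavers' period-1 endpoint is taken as known.

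1. The present ITT set drops the 4 leavers, so the estimate is 2.0.
2. With leavers kept, the period-1 mean on active is (18 × 2 + 4 × 0) / 22 = 1.64. As a period-1 contrast, the shift is 0.36.
3. The primary analysis is a crossover model with a random patient effect. The leavers have no period-2 value, so the model adjusts the sequence's period-2 placebo mean through the correlation: 0 + 0.4 × (1.636 − 2) = −0.145.
4. The active-minus-placebo difference in this sequence is 1.636 − (−0.145) = 1.782. In the placebo-first sequence it is 2.
5. The average over the two sequences is (1.782 + 2) / 2 = 1.89.

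A generalised least squares fit (SD 3, correlation 0.4, no baseline covariate) gives 1.89 averaged over periods with the treatment-by-period term, and 1.88 without it. The shift is about 0.11 days. With 2 early leavers in each sequence, only the active-first ones lacking benefit, the same fit gives 1.94 to 1.95, a shift of about 0.06.

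**The case against.** The strongest reply is that the criterion is availability of diary counts and not tolerance of the product. Study procedure requires the diary throughout the study, so a patient who stops the powder because of symptoms but keeps the diary meets the ITT definition. That stands. A reader might infer that everyone who cannot tolerate the first product is removed; the article does not say so. Only those who leave the study in that window are lost.

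Second, the rule is written identically for both sequences: a period's endpoint is imputed only after 4 weeks in that period, and an early period-2 leaver remains because a period-1 endpoint exists. This also stands as a matter of wording. The consequence still differs by allocation, as described above.

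Third, a reader might take the 0.36-day shift as the bias in the primary result, or conclude that the active product is being flattered. The article supports neither. The 0.36 belongs to a parallel-group comparison of period 1, which is not the primary analysis. The early share, the absence of benefit and the lack of placebo leavers are all assumed. Mannitol was chosen for a similar gastrointestinal profile, and the half-dose start is meant to limit early symptoms. Both features may reduce imbalance between the arms, though neither guarantees equality.

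Fourth, drop-out frequency, timing and reasons will be reported by treatment, so a differential early loss would be visible. Inverse probability of censoring weights will be considered if data appear missing not at random. These are partial safeguards: reporting does not change the estimate, and the weighting is neither committed to nor said to restore the excluded patients.

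**Conclusion.** The point holds in a limited form. The set called ITT is a modified ITT set with a post-randomisation entry condition that treatment can influence, and every planned efficacy analysis leaves out the early leavers. This follows from the definitions alone and needs no assumption.

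The numerical effect is uncertain and probably modest under the crossover model. In the scenario above, which is assumed throughout, the estimate moves from 2.0 to about 1.9 days. Neither size nor sign can be derived from the article.

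This is not a detail left to the statistical analysis plan: the article itself fixes the sets, the exclusion and the assignment of analyses. By contrast, a reader might look for a defined safety population and count its absence as part of the problem. The article sets no such restriction on the safety analysis, and that definition is commonly left to the analysis plan.

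**What to change.** - Assign the primary analysis to the full analysis set, which the article already defines.
- Extend the multiple imputation of the period-1 endpoint to patients who leave in the first 4 weeks, using the baseline count and whatever diary days exist. Changing the set without imputation would add no outcome data for them. Their period-2 endpoint stays unimputed, as already planned for other patients who leave in period 1.
- Rename the present set modified ITT (at least 4 weeks of diary data) and keep it as a sensitivity analysis beside the per-protocol one.
- Optionally, add a reference-based (placebo) imputation for early leavers on active product as a further sensitivity analysis. This is a choice, not a requirement.

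The cost is a wording change in the protocol and analysis plan, by amendment where the article's rule on deviations calls for it, and slightly more imputation work. The imputations for early leavers will rest on few diary days, and the estimate may come out slightly smaller.
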